**Study Design**

This is a cohort study to categorise the traumatic brain injury population at UHB. Brain biomarkers, serum, micro-diasylate, CSF and imaging will be measured in two groups of patients. Outcome will be assessed by TMS threshold, ERP, ERG, VEP and cognitive and psychological questionnaires will be performed. The two groups of patients will be:

The study group - patients who have suffered a head injury presenting or transferred to UHB.

The control group - patients admitted with non-head trauma matched to the study group by ISS severity and demographic.

Patients for inclusion will be identified at point of injury or as soon as possible after presentation to UHB upto 1 hour post injury. For samples taken pre-hospital where patients are unable to consent these will be taken, subject to a favourable REC opinion under the Mental Capacity Act ‘waiver’ for research in emergency situations. Advice will be sought from a consultee as soon as practicable following presentation to hospital and consent will be sought from the patient once capacity has been regained. Information in the form of the included Patient Information Sheets or Consultee Information Sheet will be provided; consent or advice will be recorded on the appropriate written forms annexes c-i.

*Inclusion criteria:*

Study group - Patients who have sustained a head injury resulting in presentation to UHB within 1 hour of injury.

Control group - non-head trauma patients matched to control by severity (ISS) and demographic.

*Exclusion criteria:*

Children under the age of 18 years. For the control group those with a recent head injury or known neurological condition.

Our conservative assumption is that 80% of head injured patients will show a positive biomarker response with 10% of non-head injured patients showing a positive response. Using fishers Exact test (power0.9; alpha 0.05; 1:1 control subject ratio) would predict 10 patients in each group. However head injuries and trauma in general demonstrates much heterogeneity and to allow comparison across modalities and sub-groups we intend to recruit up-to 100 patients to the study group and the control group.

*Sampling - Blood*

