**Methodology**

1. Patient Recruitment: All trauma patients with a survivable injury and ISS (decision) will be entered into the study. 100 trauma patients with a brain injury and 100 trauma patients without a brain injury will be studied. The study team will liaise with the emergency department at UHB for local trauma.
   1. Patient journey: Demographics will be entered into a patient database, a schedule of sampling will then be generated to allow the patient to be followed through the study.
   2. Insults: initial injury and insults - baseline GCS score, post-traumatic amnesia, surgical intervention, infection, sepsis, ICP, cerebral blood flow and oxygenation, seizure.
   3. Timings: Admission, surgery, ventilation days, ICU days, discharge, rehabilitation, time to recovery.
2. Measurements and sample collection: The following measurements will be made on samples taken from point of injury through to six month follow-up. The schedule appears in table 1.
   - 1. *Venous blood*. Venous access for drugs and fluids is gained early in trauma care at point of injury, however blood would not routinely be withdrawn as there are no useful clinical tests at this stage currently. We propose to withdraw 20mls at this point for analysis of the early biomarker milieu. An additional 20mls of venous blood will be taken at subsequent time-points. These will be analysed for biomarker levels and metabolomics. Genomic analyses will be carried out on mitochondrial and nuclear DNA, including mitochondrial DNA haplogroups, Apoliprotein E haplotypes and genes of the MToR pathway.
   1. *Micro-diasylate*. Micro-dialysis is used in routine clinical practice to monitor cerebral perfusion. The small amount of diasylate generated would normally be discarded in clinical practice, we propose to recover it for analysis. The diasylate will be snap frozen following recovery and sent to DSTL for analysis.
   2. *CSF*. Where CSF is withdrawn in normal clinical practice an additional 5 mls will be withdrawn for biomarker analysis.
   3. *Imaging.* MRI, MRS, DTI, will be performed in accordance with the schedule at table 2.
      1. MRI: T1, T2, FLAIR, DWI, ADC sequences will be acquired on a 1.5T scanner in the UHB inpatient imaging department.
      2. MRS: sequences will be acquired on a 1.5T scanner in the UHB inpatient imaging department.
      3. DTI: sequences will be acquired on a 1.5T scanner in the UHB inpatient imaging department.

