**Statistical Analysis**

Data will be analysed using SPSS. Descriptive statistics will be determined on parametric and non-parametric data. The independent variables are age, sex, ISS/NISS, type of injury, MTOR activity status. The primary dependent variables include biomarker levels, imaging analysis, TMS threshold and cognitive/psychological scoring. Exploratory assessment of data will be completed using analysis of co-variance and ordinal analysis of outcome. The spread of the means will be given as standard error of the mean. Differences in the means are considered significant if p<0.05. Psychological and cognitive scoring will undergo correlation analysis using Spearman’s rank correlation coefficient. They will also be subject to Rasch analysis. Multivariate regression analysis will be used to identify factors with significant impact on outcome.

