**Outcome Measures**

Outcome of brain trauma will be assessed with cognitive and psychological symptom scoring, TMS threshold measurement and ERP. Initial severity scoring will be assessed with ISS/NISS. Changes in biomarkers will be measured in relation to brain trauma versus non-brain trauma and related to the above outcome assessment.

The primary outcome will be functional status as measured by the Glasgow Outcome Score at 6 months. Secondary outcome measures are functional status as assessed by the Glasgow Outcome Score at 12 months; cognitive and psychological symptom scoring with Post­concussion Symptom Questionnaire­19 (PCSQ­19), Impact of Events Scale – revised (IES­r), Depression and Anxiety Symptom Scale – 21 (DASS­21), PTSD checklist (PCL), Patient Health Questionnaire (PHQ), neurological assessment battery NAB-SM.

Other seconday outcome measures are neurophysiology measures of TMS threshold and Event related potentials.

Developing a better understanding of the relationships surrounding severe brain trauma and biomarkers in development will lead to better clinical understanding, categorisation, prognostication and treatments, both in targeting existing interventions and through development of new treatment in future interventional studies.

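### Known neurological disease and recent earlier head injury bar controls but not head-injured patients, so two-group contrasts tend to count some pre-existing brain disease as an effect of the injury

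*Protocol*

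**What the plan says.** Under Exclusion criteria in the protocol's Study Design section, the only exclusion common to both groups is "Children under the age of 18 years". The next sentence applies to one group: "For the control group those with a recent head injury or known neurological condition". The study group's inclusion criterion is "Patients who have sustained a head injury resulting in presentation to UHB within 1 hour of injury", with no condition on earlier neurological history. The Methodology section is equally open: "All trauma patients with a survivable injury and ISS (decision) will be entered into the study".

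Controls are "patients admitted with non-head trauma matched to the study group by ISS severity and demographic". The Statistical Analysis section states: "The independent variables are age, sex, ISS/NISS, type of injury, MTOR activity status". The data items listed under Patient Recruitment in Methodology are demographics, the injury and the insults that follow it, and timings of care. Pre-injury neurological history appears in none of these places.

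The two groups are meant to be compared. The Outcome Measures section near the end of the protocol says: "Changes in biomarkers will be measured in relation to brain trauma versus non-brain trauma".

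**The concern.** The comparison group is screened for brain disease and the index group is not. A patient with dementia, an old stroke or epilepsy enters if the trauma includes the head, but is turned away as a control if it does not. Leaving recent head injury out of the control group is partly a matter of definition. Leaving out any known neurological condition is not: it removes from one side a characteristic that the other side may carry.

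Many of the study's measurements are ones that earlier brain disease can plausibly change: MRI, MRS and DTI findings, p300 latency, visual evoked potentials, memory and cognitive scores. No pre-injury baseline is available. The Study Design section judges neurophysiology against published norms and questionnaires against published validation populations, so an old deficit looks the same as a new one. At stake is how much of a difference between the groups can be put down to the injury.

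**Working it through.** **Is the asymmetry removed elsewhere in the protocol?**

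| Place | What it covers | Prior neurological history? |
|---|---|---|
| Study Design, inclusion of study group | head injury, presentation within 1 hour | no |
| Study Design, matching | ISS and demographic | no |
| Methodology, Patient Recruitment | demographics, insults, timings | not listed |
| Statistical Analysis, independent variables | age, sex, ISS/NISS, injury type, MTOR status | no |
| Ethical Considerations | safety screening for TMS and magnetic fields | limits who has the procedure, not who enters the study |

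It is not.

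**The plan's own figure.** Study Design assumes positive biomarker responses of 80% and 10% and derives 10 patients per group (Fisher's exact test, power 0.9, alpha 0.05). Exact enumeration gives 93.7% power at 10 per group one-sided. Two-sided, it gives 84.1% at 10 and 90.5% at 11. The figure is reproduced one-sided and is one patient short two-sided. The present point does not depend on it. What matters below is the assumed difference, 80 − 10 = 70 percentage points, and the planned maximum of 100 per group.

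**Continuous endpoints.** Assumptions, not in the documents: a share q = 5 to 15% of head-injured patients has a prior condition, no control has one, and the condition shifts the endpoint by 0.5 to 1 SD in the same direction as injury.

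- Spurious mean difference = q × shift
- Low end: 0.05 × 0.5 = 0.025 SD
- High end: 0.15 × 1.0 = 0.15 SD
- Standard error of a mean difference at 100 per group = √(1/100 + 1/100) = 0.141 SD
- Bias in standard errors: 0.025/0.141 = 0.18 to 0.15/0.141 = 1.06
- Chance of a two-sided p<0.05 when the injury has no effect: about 5.4% at the low end and about 18% at the high end, instead of 5%

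**Abnormal/normal endpoints where injury itself makes few people abnormal.** Assumptions: no injury effect, 10% abnormal without prior disease, 60% with it.

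- Spurious difference = q × (0.60 − 0.10)
- q = 5%: 2.5 points; q = 10%: 5 points
- Chance of a significant two-sided Fisher test at 100 per group: about 6% and 14%
- Beyond the 5 to 15% range, q = 20% gives 10 points and 44%; q = 30% gives 15 points and 76%

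**Biomarker positivity.** The plan takes 80% of head-injured patients to be positive already. If prior disease acts independently of the injury and would make half of its carriers positive, it can convert only the remaining 20%:

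- Spurious addition = 0.5 × 0.20 × q = 0.5 points at q = 5%, 1.5 points at q = 15%
- Against the assumed difference of 70 points, this is negligible.

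**The case against.** The strongest reply is that the two-group contrast is not the main question. The Hypotheses section is prognostic, the primary outcome is the Glasgow Outcome Score at 6 months, and the study is described as a cohort that categorises the TBI population at the hospital. Open entry of head-injured patients suits that purpose. This stands, and it limits the weight of the point. It justifies keeping these patients in the cohort; it does not justify screening only the comparator when the two are contrasted.

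A second reply is that a statistical analysis plan, not shown, might adjust for the history. It might, but only if the item is collected, and the protocol does not list it. Eligibility itself is fixed here. With no such patients among the controls, a simple adjustment for the flag also amounts to leaving the flagged patients out of the contrast.

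A reader might infer several stronger things that the documents do not support:

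- That the bias always enlarges the injury effect. This needs prior disease to shift each endpoint in the same direction as injury and to be unrelated to injury severity. If such patients tended to enter with milder head injuries, acute marker levels could be lower.
- That any earlier head injury, or retinal disease, bars a control. Only a recent head injury does, and the text does not say whether retinal disease counts as neurological.
- That removing head-injured patients with prior disease would correct an overstated specificity. Specificity depends on controls, and they stay screened.
- That biomarker positivity in the head-injured group could be inflated by 0.5 × q, or 2.5 to 7.5 points. That would hold only if the injury made almost nobody positive, whereas the plan assumes 80%.

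**Conclusion.** The exclusion criteria screen one side of a planned comparison for brain disease, and nothing in the protocol offsets this. Contrasts of head-injured patients with controls will tend to attribute pre-existing disease to the injury where the two act in the same direction. Under the assumed prevalence and shift, the effect on continuous endpoints runs from negligible (0.025 SD) to about one standard error (0.15 SD), and the documents give no basis for choosing within that range. The exposure lies mainly in the imaging, cognitive and neurophysiology contrasts. The assumed 80% versus 10% biomarker contrast would be almost unaffected. Within the head-injured group, unrecorded prior disease could also confound the relation between biomarkers and the Glasgow Outcome Score; its size cannot be worked out from the protocol. The point does not invalidate the design, but it deserves a change because the change is cheap.

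**What to change.** 1. In Methodology, add to the data collected in both groups: known pre-injury neurological condition (yes/no) and recent previous head injury (yes/no). The protocol does not define recent; use one definition for both groups.
2. In Study Design or Statistical Analysis, state that every head-injury versus control contrast leaves out head-injured patients who meet the exclusion already applied to controls.
3. Keep those patients in the cohort and in the within-group prognostic analysis, with the flag as a covariate.
4. State that any specificity estimate applies only to people without known neurological disease, since controls remain screened.

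The cost is one history item and a sentence or two of text. The history already has to be taken to screen controls. The two-group contrasts lose some head-injured patients, 5 to 15 of 100 under the prevalence assumed above, and describe a narrower population. The prognostic analysis loses nobody.

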Imaging will be performed on a random selection of patients as detailed below. MRI, MRS, and DTI sequences will be attained. The initial scans will be interpreted using the imaging findings as biomarkers for trauma. Specifically structural and micro-haemorrhages on MRI, N-acetylaspartate (NAA), choline, creatinine, myoinositol with Magnetic Resonance Specroscopy and changes in fractional anisotropy with Diffusion Tensor Imaging as a marker of axonal disruption.

*Outcome Measures*

A marked weakness in previous studies has been the lack of comprehensive outcome assessment as opposed to assessment of injury severity shortly after injury. Outcome following injuries can be very heterogeneous and prognostication is often inaccurate. For this reason all-round assessment of outcome should allow better extrapolation of the clinical usefulness of potential biomarkers.

At follow-up participants will complete a number of psychological and cognitive questionnaires to categorise various aspects of outcome following their injury. Participants will also undergo measurement of TMS motor thresholds before and after a motor learning exercise. EEG will be performed to measure p300 and VEP, ERG will be recorded.

*Cognitive and psychological questionnaires*

The complexity of the brain leads to a wide array of effects following injury. A plethora of tests have been developed to try to capture these and relate to severity of injury. We have selected short questionnaire based tests to focus on the characteristic sequelae of neuro-trauma, cognitive effects including memory, post-traumatic stress symptoms, depression and anxiety. The Test of Memory Malingering TOMM and Neurological assessment battery NAB will be used and will augment those used in routine clinical practice. Outcome will be assessed by scores against published validation populations. High scores indicating abnormality in the domain tested specific to the individual test. TOMM provides validity to other administered tests and is not an outcome measure of itself.

*Neurophysiology*

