Many techniques have been developed for and applied to the study of brain disorders and the impact on brain function. A number of neurophysiological techniques may be used to investigate specific pathways or attributes. Trans-cranial magnetic stimulation involves the use of magnetic fields to stimulate specific groups of neurons, the effect of that stimulus may then be measured, for instance in the motor cortex by electro-myogram (EMG) recording of the muscle that area represents. Responses of neurons to the stimulus can be affected by learning activities; the affect of which may be altered following brain injury. Other techniques may be used to study other brain pathways, event related potentials are generalised electrical responses of the brain to a stimulus. p300 is one such potential that may be measured by EEG recording of a subject whilst undertaking a task; the oddball paradigm is an auditory task where-by an unexpected auditory stimulus is introduced allowing the measurement of the p300 potential it triggers. These responses depend on communication between diffuse brain areas and study of them provides insights into that communication in health and disease. These principles have also been applied to the visual system, an electro-retinogram (ERG) may record the retinal response to visual stimuli and a limited version of EEG may record the response of the occipital visual centers to similar stimuli, both can provide important information regarding relevant brain areas following injury.

Outcome will be assessed by results outside of published norms. TMS measurements will look for a loss of the threshold change expected after a learning activity in those suffering the sequelae of head trauma. Outcome for event related potentials will be a delay or absence of the potential.

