   4. *Test Of Memory Malingering (TOMM).* The TOMM is administered by a trained clinical psychologist, it provides a quantification of effort and helps to validate findings of routine clinical questionnaires, it is not transparent to the participant. TOMM score sheet annex l. *Neurological Assessment Battery (NAB)*. A short version is administered which quantifies cognitive sequelae, it is in questionnaire format.
   5. *Trans-cranial Magnetic Stimulation (TMS).* This will be used to explore the neurophysiology behind how the injured brain learns using protocols that are well established and validated in healthy volunteers. Participants will undergo two bouts of single pulse TMS at frequencies no greater than 0.67 Hz before and after a period of learning. The learning task involves seating the participant in front of a computer and tasking them to track a cursor presented on the screen as accurately as possible. For each of the target lines presented, performance will be quantified as root mean square error between the actual and target traces. The change in activation threshold will be measured before and after which provides insight into the underlying changes. This will be performed at 1 year.
   6. *EEG.* The p300 event related potential will be recorded for participants using an auditory oddball paradigm. Latency will be recorded at the scalp electrode with greatest response, EEG itself is as per standard neurophysiological clinical practice. This will be performed at 1 year.
   7. *ERG*. This is recorded using a standard ISCEV protocol for flash and pattern and multifocal stimuli. Participants have three electrodes placed on the forehead and either side of the eyes and a very fine DTL loop electrode placed in the inferior conjunctival fornix which is painless. Recordings of responses to the stimuli are taken following light and dark adaptation. This will be performed at 1 year.
   8. *VEP*. A limited form of EEG is recorded over the occipital cortex to record higher level responses to flash and pattern and multi-focal stimuli, again to the ISCEV standard protocols. This will be performed at 1 year.
   9. *Pupillometry*. This utilises a device to accurately and sensitively assess the pupillary reflexes giving information on the pathways subserved. This will be performed during the first 30 days.
3. Locations:
   1. Sample collection at point of injury will be conducted by West Midlands Ambulance Service.

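### Neurophysiology outcomes are scored as outside published norms although latency is continuous and matched trauma controls are recruited, and the TMS outcome is a threshold change in one place and a threshold in another

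*Protocol*

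**What the plan says.** **Scoring rules.** In the protocol's Study Design section, the Neurophysiology part covers TMS, event-related potentials, ERG and VEP, and then states: "Outcome will be assessed by results outside of published norms". It adds: "Outcome for event related potentials will be a delay or absence of the potential". No norm limit is given. The part on cognitive and psychological questionnaires states: "Outcome will be assessed by scores against published validation populations".

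**What is measured.** For the p300, Methodology states: "Latency will be recorded at the scalp electrode with greatest response". That is a continuous value.

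**Who is available for comparison.** Study Design defines the controls as "patients admitted with non-head trauma matched to the study group by ISS severity and demographic". Clinical Setting gives them the role of the non-head-injury comparison, and Methodology plans 100 of them beside 100 head-injured patients.

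**What is analysed.** Statistical Analysis states: "The primary dependent variables include biomarker levels, imaging analysis, TMS threshold and cognitive/psychological scoring". The independent variables are age, sex, ISS/NISS, type of injury and MTOR activity status. The methods named are analysis of covariance, ordinal analysis, differences in means, Spearman correlation and Rasch analysis of the psychological and cognitive scores, and regression. ERP, VEP and ERG do not appear in that section.

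**The TMS variable.** Study Design says "TMS measurements will look for a loss of the threshold change expected after a learning activity", and Methodology also describes the change in threshold from before to after the task. The opening of Study Design and the Statistical Analysis section name only TMS threshold, and Outcome Measures lists "neurophysiology measures of TMS threshold and Event related potentials".

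**The concern.** Three things do not fit together.

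1. **Reference group.** The scoring rules for the neurophysiology and cognitive outcomes point to outside populations and give the matched controls no role. Outcome Measures states the brain versus non-brain trauma contrast explicitly only for biomarkers. If injury elsewhere in the body, or its treatment, shifts these measures, a comparison with norms alone would credit that shift to the head injury. Matched controls can separate the two.

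2. **Scale.** In or out of norm, and delayed or absent, are yes/no outcomes built from measurements that are mostly continuous. Cutting a continuous value at an extreme limit discards most of its information. The limit itself is not fixed, so it could be chosen after the data are seen.

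3. **TMS variable.** The scientific question is whether learning still changes the threshold. A single threshold measures excitability at one moment. It is a different quantity and cannot show loss of the learning response.

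**Working it through.** **The plan's own figure.** The only sample-size figure is 10 per group for biomarker positivity of 80% versus 10% (Fisher's exact test, power 0.9, alpha 0.05, sidedness not stated). Exact enumeration gives 93.7% power one-sided at 10 per group. Two-sided it gives 84.1% at 10 and 90.5% at 11. The figure reproduces one-sided and is one patient short two-sided. It does not concern the outcomes discussed here, for which the protocol gives no effect size, SD or norm limit. What follows is therefore illustrative.

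**Inputs.** From the protocol: n = 100 per group, alpha 0.05 (taken as two-sided). Assumed: a roughly normal measure, a difference d = 0.4 SD, a norm limit that cuts off the upper fraction c of the controls, and no dropout.

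**Continuous comparison with the controls.** Power = Φ(d/√(2/n) − 1.96) = Φ(0.4/0.1414 − 1.96) = Φ(0.868) = 81%.

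**The same data as abnormal yes/no.** The abnormal share is c in controls and p = 1 − Φ(z(1−c) − 0.4) in head-injured patients. Power = Φ((p − c − 1.96·SE0)/SE1), with SE0 = √(2·p̄(1−p̄)/n), SE1 = √((p(1−p) + c(1−c))/n) and p̄ the mean of p and c.

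| Norm limit c | Abnormal, head injury | Power at 100 per group | n per group for 90% power |
|---|---|---|---|
| 2.5% | 5.9% | 23% | 717 |
| 5% | 10.7% | 32% | 472 |
| 10% | 18.9% | 43% | 326 |
| 16% | 27.6% | 51% | 264 |
| continuous | n/a | 81% | 132 |

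For c = 2.5%: p − c = 0.0344, SE0 = 0.0284, SE1 = 0.0283, so power = Φ(−0.75) = 23%. With d = 0.3 the fall is from 56% to 14-31%, and with d = 0.5 from 94% to 34-71%.

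**Norms as the only reference.** Suppose non-head trauma alone shifts a measure by 0.3-0.5 SD (assumption). The share of controls beyond a limit meant to flag 2.5% is then 1 − Φ(1.96 − 0.3) = 4.8% to 1 − Φ(1.96 − 0.5) = 7.2%. In head-injured patients the same excess would be read as brain injury unless the controls are used.

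**TMS: change against a single threshold.** The SD of a change is SD·√(2(1−ρ)), where ρ is the pre/post correlation, which is not given. For a shift of 0.4 SD in the post-learning threshold and none before learning, the single threshold has 81% power. The change has 67% at ρ = 0.3, 81% at 0.5, 95% at 0.7 and above 99% at 0.9. Power thus has no fixed direction; what differs in every case is the quantity estimated.

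**The case against.** **No dichotomised analysis is actually specified.** Statistical Analysis plans means, covariance analysis and rank correlation, which are not how a yes/no flag is handled. Scores set against validation populations may simply mean standardised scores. Referring an individual to norms also suits a study that seeks prognostic information for individual patients. For cognitive scores and TMS threshold this largely stands: the fault there is two descriptions left unreconciled. It stands less well for ERP, VEP and ERG, which Statistical Analysis never names. Its list of variables is open-ended, so a comparison of means could be extended to latency, but nothing says so, and the norms rule is the only one written.

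**The controls are not lost.** A reader might infer that the trauma control is abandoned for these outcomes. The protocol does not support that. Type of injury is an independent variable, and no passage excludes controls from outcome testing. What is missing is a stated role for them in scoring these outcomes.

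**The loss may be smaller.** One could calculate that 100 patients are worth only 14-22, from the efficiency φ(z)²/[c(1−c)] = 0.14 at c = 2.5% and 0.22 at 5%. That needs very few abnormal results in the analysed sample. If 20-30% of head-injured patients were abnormal (assumption), the same formula gives 0.49-0.58 for relating biomarkers to outcome. The figure depends on a limit and an analysis the protocol does not fix.

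**TMS threshold may be shorthand.** The descriptive text consistently measures before and after learning, so a deliberate switch to a raw threshold is not shown. Nor is a loss of power, since ρ is unknown. The inconsistency between the sections remains.

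**The norm populations are not described.** Whether they included trauma patients cannot be settled from the protocol, so the bias argument is conditional.

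**Conclusion.** The point holds in limited form.

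- For ERP, VEP and ERG, the only stated outcome rule is a norm-based one. It does not use the continuous measurement, gives no limit and assigns no role to the matched controls.
- For cognitive scores, the norm-referenced wording and the score-based analyses need to be reconciled.
- For TMS, the protocol defines a change and then lists a threshold; these answer different questions.

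If the norms rule is followed, power at 100 per group falls from 81% to 23-51%. This rests on d = 0.4, normal data, limits at the upper 2.5-16% and no dropout, none of which the protocol gives. Attribution of general trauma effects to brain injury is possible, but its size is unknown. The protocol does not establish that every outcome will be dichotomised, that the controls are discarded, or that the TMS wording costs power.

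The consequence is bounded. Outcome Measures makes the Glasgow Outcome Score at 6 months primary and the cognitive, TMS and ERP measures secondary, and does not list VEP or ERG at all. Even so, Statistical Analysis counts TMS threshold and cognitive scoring among its primary dependent variables. The correction is worth making because it costs almost nothing.

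**What to change.** 1. In the Study Design parts on questionnaires and neurophysiology, and in Statistical Analysis, state that p300 latency, VEP and ERG values and cognitive scores are analysed on their own scale. The comparison is head-injured patients versus the study's matched controls, with the covariates Statistical Analysis already lists (age, sex and ISS/NISS among them). An absent p300 takes the worst rank in a rank analysis. Published norms are used only to describe results.

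2. In the opening of Study Design, in Statistical Analysis and in Outcome Measures, replace TMS threshold with *pre-to-post-learning change in TMS threshold*. This is the variable the protocol already defines. Post-learning threshold adjusted for pre-learning threshold is a less safe choice here. The groups are not randomised and the pre-learning value is itself measured a year after injury, so adjusting for it may answer a different question.

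**Cost.** Wording and a small amount of extra analysis. No new patients or measurements are needed, provided the controls undergo the same outcome tests, which the protocol nowhere rules out. Labelling individuals as normal or abnormal becomes less direct, but the descriptive use of norms keeps it available.
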